## Abstract

**Background:**

One central goal of physical education in many countries is to empower students to be physically active throughout their lifespan. Physical activity-related health competence (PAHCO) encompasses physical, cognitive, and motivational elements associated with the individuals’ ability to be physically active in a health-enhancing way. To date, there is a lack of empirical evidence concerning effective programs and methods to promote PAHCO in physical education. The purpose of this study is to examine to what extent a health and physical fitness-related program that includes learning tasks integrating theoretical and practical elements promotes students’ PAHCO in physical education.

**Design/methods:**

This study is a cluster randomized controlled trial that compares two physical education intervention programs on health and physical fitness (IG-run, IG-game play) with regular physical education lessons (CG-run, CG-game play) in secondary schools in Germany. Forty-eight physical education classes (ninth grade) were recruited and randomly allocated to the four study groups. The intervention programs include six physical education lessons on health and physical fitness and only differ in the type of physical activity that is executed (running and jumping vs. small-sided games). The students’ PAHCO is examined both pre- and post-intervention and after 8–12 weeks of follow-up. We also determine various process variables during the intervention period to analyze the intervention fidelity.

**Discussion:**

The results of this study provide evidence on whether a combination of theoretical and practical elements in physical education can enhance students’ PAHCO. Beyond that, our process analyses will allow differentiated insights into the mechanism of how the intervention programs work.

**Trial registration:**

German Clinical Trials Register (DRKS), DRKS-ID: DRKS00016349. Retrospectively registered on 10 January 2019.

**Electronic supplementary material:**

The online version of this article (10.1186/s12889-019-6686-4) contains supplementary material, which is available to authorized users.

## Background

The enhancement of students’ knowledge, understanding, skills, and motivation to enjoy a (healthy) physically active lifestyle throughout the lifespan has been acknowledged as a central goal of physical education (PE) in many countries (e.g. [1, 2]). The main goal of the project GEKOS (Förderung bewegungsbezogener Gesundheitskompetenz im Sportunterricht) is to investigate the impact of a health and physical fitness-related PE program that combines practice and theory on physical activity-related health competence (PAHCO) in lower secondary students. In recent years, various school-based intervention studies aimed to promote students’ health or physical fitness, increase their physical activity (PA) level, or affect the psychological determinants of PA (e.g., knowledge, motivation, attitudes towards PA) [3, 4]. According to a review by Demetriou and Höner [5], school-based interventions that include a PA component can significantly affect students’ physical fitness level (70% of the reviewed studies) or PA behavior (57% of the reviewed studies). In addition, this review demonstrated that considerably more intervention studies have examined the effect on physical fitness (51%) or PA (57%) than on different psychological determinants of PA (e.g., knowledge, attitude (12%)). When psychological determinants were investigated, intervention studies reported an entirely positive impact upon students’ knowledge (87%), whereas the effects on other psychological determinants varied between the studies. Moreover, most of the studies did not analyze the intervention effects on PA, physical fitness and health, or psychological determinants at the same time (84%). Further, only 8% of the included studies were rated as high quality methodological studies (e.g., 16% of the reviewed studies included a follow-up measurement to determine long-term effects, only 32% randomized students into different study conditions). In addition, only a minority of studies provided a theoretical foundation (21%, e.g., social-cognitive theory), reported on the quality of intervention delivery, or analyzed the underlying mechanism how the respective effects of an intervention program were evoked (e.g., using a process analysis). However, differentiated analyses of effects and processes are necessary to identify differential effects in subgroups or to be able to accurately interpret possible mechanisms underlying the interventional effects [6, 7]. For example, in a PE health promotion program with strength and endurance exercises, process analyses showed that boys complained about the lack of ball games. Beyond that, they reported that they had less fun in PE during the health promotion program than girls compared with regular PE. The different acceptance of the health promotion program in this study was associated with higher benefits on girls’ than on boys’ physical fitness [3, 8]. These findings raise the question of gender-specific effectiveness of health promotion programs in PE.

Against this background, we designed the current study as a cluster randomized controlled trial with follow-up measurements aiming to promote competences for a healthy, physically active lifestyle. In most Anglo-Saxon PE-curricula, physical, cognitive, and motivational elements associated with a physically active lifestyle are described by the concept of physical literacy (e.g., [1, 9]). At the same time, physical literacy is the main purpose of PE in many countries [10]. PE curricula in Germany (e.g., [11]) aim to achieve the goal of a physically active lifestyle by fostering a variety of different competences (e.g., movement competence) as well as by considering the different values concerning PA as “the value of health and physical fitness”.^1^ In recent years, researchers from different fields have developed competence models dealing with health and physical fitness issues related to PA (e.g., [12, 13]). These models are compatible to physical literacy and health literacy concepts especially in Anglo-Saxon regions representing the intersection of both concepts [14, 15]. In concrete terms, they focus on knowledge, skills, motivation, and abilities considered important to initiate and maintain health-enhancing PA behavior.

The forthcoming trial aligns to the PAHCO model by Sudeck and Pfeifer [13]. It encompasses three sub- competences (movement, control, and self-regulation competence) that are built on different elements among cognitive, physical, and motivational domains. Of these, particularly control competence needs to be highlighted as it plays a central role in being physically active and engaging in PA in a health-enhancing way. Therefore, control competence not only has an effect on the quantity but especially on the quality of PA (e.g., in terms of optimizing health benefits of PA). The mentioned sub-competence can be further divided in two sub-facets focusing on physical health (control competence for physical training) and subjective well-being (control competence for PA-specific affect regulation). This study targets particularly control competence for physical training and the underlying elements of the cognitive domain (health-related fitness knowledge), physical domain (physical fitness) as well as motivational domain (interest and attitudes). Individual control competence for physical training depends on ones understanding of health-related fitness knowledge and its appropriate application to gear PA to individual health. Furthermore, it is related to the ability to be aware of body signals and to use these to control physical load. Summarized, control competence for physical training is not only affected by mere knowledge but also by an understanding and appropriate application of this knowledge in order to adjust actual PA with the goal of promoting health (and well-being) [13]. Hence, a combination of teaching knowledge and PA-related skills and abilities are required for the acquisition of PAHCO in particular for control competence. Studies, which investigated different health behaviors based on the information-motivation-behavioral skills model, support this assumption by demonstrating a relationship between behavior-specific information and behavioral skills that are associated with a specific health behavior [16, 17]. Further, e.g., Fisher and colleagues [18] assumed that in turn the experience of positive health outcomes supports knowledge acquisition and motivation. This finding is in line with pedagogical assumptions that the perception of experiencing training and physical fitness also supports knowledge acquisition and motivation [19].

In Germany, there are examples about how to teach health-related contents in PE [20, 21]. However, there is a lack of research on how to promote PAHCO including not only the improvement of motor skills and abilities but also cognitive-based competence facets.

The linkage of practice (performing PA) and theory is discussed as a constructive method to teach competences in PE [22]. The use of reflective practice, that means conscious reflection-in-action or reflection-on-action, is a particular method to combine theory and practice [23]. In addition, in educational literature, particular learning tasks are attributed to enhance students’ competence. These tasks are cognitively activating, differentiate by students’ ability and facilitate interaction between students [24].

The primary aim of this study is to evaluate the impact of two health and physical fitness-related programs on the acquisition of PAHCO compared to a control group in PE. The two interventions include the same topics (health and physical fitness) as well as methodological concepts and only differ regarding the type of PA that is used to pass on the programs’ content to the students: Running and jumping activities were chosen as a more common type of PA in the context of promoting health and physical fitness, whereas small-sided (ball) games were selected to consider possible gender-specific preferences of PA [3, 25]. Moreover, small-sided games are also appropriate to promote physical fitness and health in youth [26, 27]. Additionally, process analyses are included in the trial to assess the fidelity and quality of intervention delivery, to clarify causal mechanisms, and to identify contextual factors associated with any variations in outcomes [6, 28–30]. Process analyses and intervention programs were developed and tested in two pilot studies (Pilot Study 1, Pilot Study 2) that are also outlined in this study protocol.

### Objectives of GEKOS

Predominantly, GEKOS investigates whether 6-week intervention programs called “run”/“game play” (running and jumping/small-sided ball games with a focus on health and physical fitness) lead to a higher control competence for physical training in ninth grade students as well as of health-related fitness knowledge (cognitive domain) compared to regular PE lessons in control groups “run”/“game play” (running and jumping/games). Additionally, the PAHCO model proposes that there are effects on physical fitness (physical domain) as well as on health and physical fitness-related interest and attitudes (motivational domain). In line with the rationale for the evaluation of complex interventions [28], this study includes multiple outcomes with respect to the acquisition of competence and associated cognitive, physical, and motivational elements.

Further, in accordance with previous study results, it is assumed that the positive effects of the run/game play intervention upon outcomes are moderated not only by gender but also by interest in the run/game play intervention content on the student level, which, in turn, is also assumed to correlate with gender [3, 8].

In line with Fisher et al. [18] and Baschta and Thienes [19], we hypothesize that the effectiveness of the run/game play intervention for control competence for physical training, health related-fitness knowledge (cognitive domain), and health and physical fitness-related interest and attitudes (motivational domain) would be mediated by students’ (perceived) physical fitness.

We use fidelity measures (as part of the process analyses) to investigate how the core components of the run/game play intervention are delivered and as to whether the control group teachers implement the specifications as laid out in the fidelity protocol. This procedure allows us to accurately interpret the treatment effects [6, 7]; the particular aims concerning intervention fidelity are as follows:To examine the associations between the quality of the intervention delivery and the outcome measures.To investigate the impact of teachers’ attitudes concerning the core components of the run/game play intervention upon the quality of the intervention delivery.To determine to what extent students’ perception of the intervention’s core components mediate the intervention effects on the outcomes and also to investigate the moderating role of learning motivation.To assess which student characteristics impact student responsiveness (learning motivation, acceptance, and evaluation).

In addition, we analyze the duration and intensity of PA to gain deeper insight into the teaching processes of both the intervention and control groups. This process allows us to investigate the implications of integrating theoretical contents in PE.

## Methods

### Design

The GEKOS study is a cluster randomized controlled trial that includes two intervention groups (IG-run, IG-game play) and two wait-list control groups (CG-run, CG-game play). The study is designed to investigate the superiority of an intervention compared to a control condition. Overall, we recruited 48 ninth grade PE classes and their PE teachers for this study. At this age, boys and girls in the federal state of Baden-Wuerttemberg (Germany) take separate PE classes, so we studied 24 male classes and 24 female classes. We randomly allocated the participating classes to the different study conditions stratified by gender. In order to gain more information about the quality of the intervention delivery, the relative number of classes differed between IG and CG. Accordingly, 14 classes were planned to be allocated to each intervention group prior to the intervention study, whereas 10 classes were to be placed into each control group. Further, teachers were not blinded to the study conditions as they received instructions about the intervention and control conditions prior to the study. Figure 1 illustrates the number of classes (c) and students (*n*) planned to be allocated to the different study conditions.

**Fig. 1 Fig1:**
[figure not shown]
The study design containing the planned number of classes and students prior to the study

Over the course of the study, students are tested pre-intervention, post-intervention, and after 8–12 weeks follow-up during their regular school lessons (Fig. 1). The post-intervention and follow-up times may vary for organizational reasons (e.g., school holidays, examinations, canceled lessons). To evaluate the intervention delivery and the students’ duration and intensity of PA, several process variables are assessed during the intervention period. To realize the intervention and comprehensive assessments across 48 classes, the study is carried out in three waves (Wave 1: 1st semester 2017/2018, Wave 2: 2nd semester 2018, Wave 3: 1st semester 2018/2019).

The present study protocol adheres to the Standard Protocol Items: Recommendations for Intervention Trials (SPIRIT) guidelines [31]. The SPIRIT Checklist is provided as supplementary material (see Additional file 1).

### Study setting and participants

Ninth grade PE classes with their respective teachers across secondary schools (Gymnasium) take part in the study. In order to be eligible for the study, PE classes had to fulfill a range of inclusion criteria: the school principal had to approve study participation; PE teachers must have completed their respective degrees; participating students had chosen majors other than PE; and classes had to be located in Baden-Wuerttemberg, Germany.

### Recruitment

The heads of the regional school boards of Baden- Wuerttemberg were the main gatekeepers for recruitment. In preparation for each study wave, we asked the heads of the school boards three to four months in advance to contact the school principal and the teachers who are responsible for PE at their schools (PE subject coordinators) and to invite them to participate in the study. Additionally, the main researchers contacted PE teachers at schools that participated in pilot studies and also former PE students at a University in Germany. During recruitment, interested PE teachers received detailed descriptions of the study and an information sheet to share with their school principals. We informed those who agreed to participate in the study about group allocation as soon as we completed our randomization procedures. These teachers also received informed consent forms for their students and a timetable with the proposed measurement points for the pre-, post-, and follow-up assessments. We used the same recruitment process for all three study waves.

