### Randomization

We randomly assigned participants to either the control (CG-run, CG-game play) or the experimental conditions (IG-run, IG-game play). Due to gender-segregated PE classes in Baden-Wuerttemberg, we conducted separate randomization procedures within the gender strata. This investigation had three study periods (Waves 1–3); therefore, we designed the randomization procedure to be performed in three blocks of 16 PE classes. The allocation ratios differed between these three study periods. In Waves 1 and 3, we randomly and equally allocated both male and female PE classes to the four study groups (1:1:1:1). For Wave 2, we used unequal allocation at a ratio of three (IG-run): three (IG-game play): one (CG-run): one (CG-game play). The randomization took place prior to each study period according to the guidelines of Hutchinson and Styles in 2010 [32]. An independent staff member who was not involved in this study used a computer to generate random numbers for each PE class separated by gender and then sorted the cases according to their random numbers. As a result, the allocation to the different study groups remained concealed to the researchers. Table 1 summarizes the allocation ratios as well as the planned number of female and male PE classes separated by study wave.

**Table 1 Tab1:** The planned and effective allocation of the study groups separated by gender and wave

	Allocation ratio and planned number of PE classes		Effective allocated number of participating PE classes after randomization (number of participating students)									
			Male					Female				
Wave	IG-run : IG-game play : CG-run : CG-game play	male/female classes	IG-run (n)	IG-game play (n)	CG-run (n)	CG-game play (n)	Total	IG-run (n)	IG-game play (n)	CG-run (n)	CG-game play (n)	Total
Wave 1	1:1:1:1	8/8	2 (24)	2 (30)	2 (24)	2 (33)	8	2 (45)	2 (34)	2 (25)	2 (31)	8
Wave 2	3:3:1:1	8/8	2 (33)	2 (41)	0 (0)	1 (23)	5^a^	3^b,c^ (56)	2^b^ (39)	0^b^ (0)	1 (24)	6
Wave 3	1:1:1:1	8/8	3 (55)	2 (35)	3 (50)	3 (63)	11^d^	2 (42)	3 (57)	3 (51)	2 (45)	10^d^
Sum		48	7 (112)	6 (106)	5 (74)	6 (119)	24	7 (143)	7 (130)	5 (76)	5 (100)	24

^a^As the recruitment rate had been lower than expected, randomization was conducted with five classes and three additional dummy classes to compensate for the absent three male PE classes

^b^After randomization three female classes allocated to IG-run, IG-game play and CG-run canceled their participation. Therefore, they are not considered in the labeled columns

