
^c^One female PE teacher could be recruited after randomization. She was allocated to the group of PE teacher who canceled her participation at first (IG-run)

^d^In addition to the listed number of PE classes one male and two female dummy classes were added to randomization to guarantee equal allocation ratio

In Wave 2, we were unable to recruit the intended number of PE classes (8 female and 8 male PE classes). Prior to the study period 2, only 8 female and 5 male PE classes indicated their willingness to take part in this study. Therefore, only 13 PE classes were considered in the randomization. In addition, after we had completed the randomization process, three female PE teachers withdrew their participation. To compensate, another female PE teacher who agreed to take part in the study was allocated to the respective study group. Consequently, only 11 of the 16 expected PE classes (5 male and 6 female PE classes) participated in Wave 2. Once Wave 3 began, we recruited 21 PE classes (10 male and 11 female PE classes) to compensate for the absent PE classes in Wave 2 and also to reach the goal of 48 PE classes. To maintain an equal allocation ratio, we added three dummy PE classes (2 male and 1 female classes) for the randomization process. As a consequence, the effective number of PE classes varied between 2 and 3 classes per group. Table 1 shows the final result of the randomization process.

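### Student consent forms went out through teachers who knew, or were being told, their class's arm, so students could be selected by arm, and the planned model adjusts only for the outcome's own pretest

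*Protocol article*

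**What the plan says.** Four statements in the protocol article bear on the order of events.

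- Recruitment, on allocation: "We informed those who agreed to participate in the study about group allocation as soon as we completed our randomization procedures".
- Recruitment, next sentence: "These teachers also received informed consent forms for their students and a timetable with the proposed measurement points". The section closes with "We used the same recruitment process for all three study waves".
- Design: "teachers were not blinded to the study conditions as they received instructions about the intervention and control conditions prior to the study".
- Randomization, after describing an independent staff member who generated and sorted random numbers for the classes: "As a result, the allocation to the different study groups remained concealed to the researchers".

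Randomization also records changes in class entry once allocation was known. In Wave 2, "After randomization three female classes allocated to IG-run, IG-game play and CG-run canceled their participation", and one teacher recruited late was placed directly in IG-run.

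Data analysis describes linear regressions with the outcome's pretest as covariate and an intervention dummy, run separately for the run and the game-play comparison. It compares intention-to-treat with complier average causal effects, and it announces descriptive recruitment and dropout rates and baseline distributions, with reporting under CONSORT for cluster trials.

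**The concern.** Classes were randomised, but the students analysed are those who consented within each class. If consent is sought by someone who knows the arm, the mix of consenting students can differ between arms even when the allocation of classes was sound. Randomising classes gives no protection against this.

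The outcomes most exposed are the self-reported ones: control competence for physical training, interest and attitudes. Willingness to take part plausibly relates to interest in sport and fitness, and under Objectives the article itself expects interest to moderate the intervention effect.

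Nothing in the described analysis is aimed at this. Intention-to-treat and complier analyses both start from enrolled students. The missing-data paragraph covers absence on test days and loss to follow-up, not non-consent. The pretest covariate helps only as far as the pretest captures the selection.

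**Working it through.** **1. Order of events.** Put side by side, the Recruitment sentences give: the teacher agrees, the class is randomised, the teacher is told the arm, and the same teacher also receives the student consent forms. The text does not date the forms, so what it supports is with or after disclosure. The risk is the same in either case. No section shown fixes the student list or consent before disclosure.

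**2. What concealment covers.** The Randomization sentence is limited to the researchers and to the allocation of classes. Design openly says that teachers were unblinded. The two do not conflict, but neither protects student entry.

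**3. What Table 1 can show.** Participating students and classes, summed over waves and gender:

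| Arm | Students / classes | Per class | Waves 1 and 3 only |
|---|---|---|---|
| IG-run | 255 / 14 | 18.2 | 166 / 9 = 18.4 |
| CG-run | 150 / 10 | 15.0 | 150 / 10 = 15.0 |
| IG-game play | 236 / 13 | 18.2 | 156 / 9 = 17.3 |
| CG-game play | 219 / 11 | 19.9 | 172 / 9 = 19.1 |

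The total is 860 / 48 = 17.9 per class, or 69% of the planned 26. The run comparison has fewer students per class in the control arm and the game-play comparison has more. Class rolls are not given, so roll size and consent rate cannot be separated.

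**4. Illustrative size before adjustment.** Assume that the students most willing to take part are those who consent, and that willingness correlates r with the outcome. With consent rate p, the mean of those who enter shifts by r × φ(z_p) / p, where z_p is the standard normal quantile at p and φ the normal density.

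| p | z_p | φ(z_p) | φ(z_p) / p |
|---|---|---|---|
| 0.80 | 0.842 | 0.280 | 0.350 |
| 0.65 | 0.385 | 0.370 | 0.570 |
| 0.85 | 1.036 | 0.233 | 0.274 |
| 0.60 | 0.253 | 0.386 | 0.644 |

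The difference between arms, with r assumed to be 0.2 to 0.4:

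- 80% v 65%: 0.570 − 0.350 = 0.220; times 0.2 to 0.4 gives 0.04 to 0.09 SD.
- 85% v 60%: 0.644 − 0.274 = 0.370; times 0.2 to 0.4 gives 0.07 to 0.15 SD.

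**5. After the planned pretest adjustment.** Suppose willingness correlates equally with pretest and post-test, and both have the same variance. The raw gap Δ is then present at both times, and the adjusted gap is Δ − ρΔ = (1 − ρ)Δ, where ρ is the pre-post correlation. The article does not give ρ; 0.5 to 0.7 is assumed.

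- Smallest case: 0.044 × 0.3 = 0.013 SD.
- Largest case: 0.148 × 0.5 = 0.074 SD.

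The range is about 0.01 to 0.07 SD. Against the target of d = 0.30 under Sample size, the largest case is 0.074 / 0.30 = 25%. Before adjustment it is 0.148 / 0.30 = 49%.

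**6. Direction.** In this model the arm with lower consent is the more strongly selected. With r positive, lower consent in a control arm would raise the control mean and work against the intervention; lower consent in an intervention arm would do the reverse. Since consent rates by arm are unknown, so is the sign.

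**The case against.** The case against is substantial, and it limits the point in five ways.

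- **Timing is inferred.** It rests on sentence order and the word also. Consent pages are absent from the text reviewed, so a fuller statement may exist. If it dates student consent before disclosure, the point falls away. This stands, and is why the claim is confined to what the text indicates.
- **Concealment.** A reader might infer that the concealment statement is false. It is not: it is limited to the researchers, and teacher unblinding is declared. It needs a qualification, not a retraction.
- **Table 1.** A reader might take 18.2 v 15.0 students per class, or Wave 1 females at 22.5 v 12.5, as evidence of differential consent. The documents do not support that. The second contrast is two classes per arm, Wave 1 males are identical at 12.0 v 12.0, game play goes the other way, and rolls are unknown.
- **Size.** A reader might quote a bias of up to half the target effect. That is the raw shift at the extreme of the assumptions and ignores the pretest covariate.
- **Reporting.** A reader might say that recruitment will not be examined at all. Data analysis does announce descriptive recruitment rates. It does not name consent by arm, and such table detail may sit in an analysis plan not shown.

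It can also be argued that the motive for differential consent is weak, since both conditions run in ordinary lessons and consent may concern only the measurements. That is plausible but cannot be checked here. None of this removes the stated procedure of handing student consent forms to teachers who knew, or were learning, their arm.

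**Conclusion.** The point holds as a risk arising from a stated procedure, not as demonstrated bias. Student consent appears to have been sought through unblinded teachers with or after disclosure of allocation, and concealment covered only the generation of the class allocation. The planned model reduces any resulting bias through the pretest but may not remove it.

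The residual illustration of about 0.01 to 0.07 SD, at most a quarter of the target effect, rests on four assumptions: the consent rates, the correlation of 0.2 to 0.4 between willingness and outcome, the pre-post correlation of 0.5 to 0.7, and equal correlation of willingness with pretest and post-test. If willingness relates more strongly to the post-test than to the pretest, the residue is larger. The direction cannot be stated. This merits a cheap strengthening of the analysis and reporting; it does not discredit the trial.

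**What to change.** Trial status says that recruitment, randomization and baseline are complete, so the procedure cannot change. Its consequences can still be handled before the final data are analysed.

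1. Prespecify, for both comparisons, an additional analysis adjusting for the pretest plus baseline values of interest in endurance, strength and ball games, BSA-F activity, perceived fitness and BMI percentile. Run it unconditionally and report it beside the main estimate. It should not be triggered by observed consent rates, because that would make the choice of estimate depend on the data. Use baseline values only, since perceived fitness is also a proposed mediator.
2. Report consenting students as a share of the class roll by arm, wave and gender. The attendance lists may not include non-consenters; if so, obtain the rolls from the schools or teachers.
3. Qualify the Randomization sentence to say that concealment applied to generation of the class allocation, and state when student consent was obtained relative to disclosure.

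The cost is a few more covariates, one roll count per class and two clarified sentences. No new students or measurements are needed. The added covariates address only measured differences, so unmeasured motivation to take part would remain a limitation to state.
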